**Missing data**

In cases where the prescription end date is not available, we will utilise daily dosages and the quantity prescribed to calculate the duration of treatment. If this information is missing, we will impute median values for exposure duration. It is important to note that missing data on baseline characteristics will not impact the analysis because the SCCS design uses each patient as their own control. Therefore, any potential differences in baseline characteristics are inherently accounted for within the study design.

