**Methods**

**Study design**

We will apply the self-controlled case series (SCCS) study design in the proposed study.^25^ The analysis will be conducted on a population of individuals who had experienced both the outcome(s) and exposure of interest, which will be prescription of gabapentinoids. Incidence rate ratios (IRRs) will be calculated by comparing the event rates during periods of gabapentinoid exposure to the rates during all other observed time periods, in other words without gabapentinoid exposure. This will be accomplished using conditional Poisson regression.

This design has a significant advantage over the classical cohort design as included participants will act as their own control and it consequently addresses all potential time-invariant confounding effects that vary between individuals, such as genetic factors and socioeconomic factors.^26^ Additionally, we will account for time-varying factors, such as age and season, which can influence the prescription of gabapentinoids. We will also adjust for the concurrent use of other medications as time-varying factors. Sub-group analysis will also be performed for patients who suffer from mental illnesses, type 2 diabetes or cardiovascular diseases.

This method can investigate associations between acute outcomes and transient exposures^26^ and has been used extensively in literatures studying the safety of psychotropic medications and outcomes such as suicide attempts, self-harm and risk of seizure.^20,27-29^

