**Exposures**

Prescriptions of gabapentin (Anatomical Therapeutic Chemical code N03AX12) or pregabalin (N03AX16) will be identified in CPRD. The exposed period is defined as the time receiving the medication, calculated with the prescription information in CPRD (daily dosages and quantity prescribed).

The index date is defined as the first date of prescription of gabapentinoid medication. We will calculate the length of exposure using information on prescription date and prescribed days in the database. Patients will contribute to consecutive exposure risk periods while they were continuously exposed to the drug.

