**Selection of comparison group**

Included patients will serve as their own control in this study design.^26^ Eligibility will be assessed based on the inclusion and exclusion criteria outlined in the section “Definition of the Study population”. The major advantage of SCCS over the classic design is that it controls for potential effects of measured and unmeasured time-invariant confounders that vary between individuals (i.e. genetic factors, disease severity, and socioeconomic factors).

A 90 days pre-exposure period will be included into the study. Calculation of the IRR during this period of time will be performed to evaluate whether outcomes of interest were caused by the conditions that gabapentinoids prescribed for instead of the use of gabapentinoids, which in turn may introduce bias into the risk estimate during treatment.

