**Sample size consideration**

With an estimated IRR=1.5, n=484 is required with 5% level of significance and 80% power.^30^ The above sample sizes will be enough to study the outcomes with an incidence as low as 0.1%.

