A series of sensitivity analyses will be performed, including a spline-based self-controlled case series analysis, exclusion of patients who died within 6 months of the event, starting follow-up from the first neuropathic or chronic pain diagnosis, restricting to individuals with at least two gabapentinoid prescriptions, varying the length of the pre-treatment period, adjusting only for age and season, extending treatment periods. Self-controlled case series extensions analyses will also be conducted.^34^ A negative control analysis will be performed to explore residual confounding. An additional case-case-time-control analysis^35^ is to validate the main findings, in which the 30 days before the event served as the hazard period and were compared with four randomly selected 30-day reference periods 61 to 180 days earlier, future cases occurring 180 to 360 days later were matched by age, sex, and ethnicity, and adjusted odds ratios (aORs) were estimated using conditional logistic regression. A two-sided significance level of 5% was used for all analyses.

For data analysis, we will utilise either the Statistical Analysis System (SAS) or R programming software.

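### When a prescription has neither a recorded length nor a daily dosage, the plan imputes a median duration and does not say that a recorded quantity is used

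*Protocol*

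**What the plan says.** Two sections of the protocol define exposed time.

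- **Exposures.** The on-drug period is "calculated with the prescription information in CPRD (daily dosages and quantity prescribed". The same section also says that length is worked out from the prescription date and the days prescribed.
- **Missing data.** Where no end date is recorded, "we will utilise daily dosages and the quantity prescribed to calculate the duration of treatment". The last resort follows: "If this information is missing, we will impute median values for exposure duration".

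Read together, there are three steps: a recorded end date or prescribed days, then dosage with quantity, then a median duration.

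Three other statements determine where misplaced days go:

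- **Study design.** IRRs come from "comparing the event rates during periods of gabapentinoid exposure to the rates during all other observed time periods".
- **Selection of comparison group.** "A 90 days pre-exposure period will be included into the study", with its own IRR.
- **Statistical Analysis.** The sensitivity analyses include "adjusting only for age and season, extending treatment periods". The length of the extension is not given.

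**The concern.** Step two needs both dosage and quantity, and the fallback replaces the result (duration) rather than the missing input (dosage). A prescription with a known quantity but no dosage is therefore not handled in a way that uses the quantity. The wording for what must be missing can be read in two ways:

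- If it means either item, a recorded quantity is set aside.
- If it means both items, a prescription with quantity alone has no rule.

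On neither reading does the quantity inform the duration.

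Quantity carries information on supply length. A single median shortens every supply above it and lengthens every supply below it. Exposed time underlies every gabapentinoid contrast in the self-controlled case series: the main IRRs, the stratification by type of gabapentinoid, the combined windows with opioids or benzodiazepines, and the gabapentin-only against pregabalin-only comparison. The protocol's hypothesis is that exposure raises risk. If so, on-drug days counted as reference raise the reference rate and understate harm.

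**Working it through.** The plan has no figure for this rule to reproduce: it gives neither the median, nor the supply mix, nor the share of prescriptions that reach the fallback. The check is an expected-events calculation on assumed inputs.

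**Assumed inputs.** Supplies of 7, 14, 28, 56 and 84 days with shares 10, 10, 50, 20 and 10% (median 28). True IRR 1.5, the value in Sample size consideration. True exposed share of time *r* from 0.115 to 0.50. Share *m* of prescriptions given the median. Rates constant within exposed and unexposed time.

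**Step 1: days moved per prescription.**

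- Mean true supply: 0.1×7 + 0.1×14 + 0.5×28 + 0.2×56 + 0.1×84 = 35.7 days.
- Mean after capping at 28: 0.7 + 1.4 + 14 + 5.6 + 2.8 = 24.5 days. Loss: 11.2/35.7 = 31.4% of exposed time if every prescription is imputed.
- Mean over-extension: 0.1×21 + 0.1×14 = 3.5 days, or 9.8%. This counts only where no further prescription follows, because a repeat prescription absorbs it.

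So the share of exposed time lost is L = 0.314*m*. The false exposed time, as a share of true exposed time, is between A = 0 (all absorbed) and A = 0.098*m* (none absorbed).

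**Step 2: observed IRR.**

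- Exposed rate = [1.5(1−L) + A] / [(1−L) + A]
- Reference rate = [(1−r) + 1.5rL − rA] / [(1−r) + rL − rA]
- Observed IRR = exposed rate / reference rate

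Example, *m* = 0.10, *r* = 0.50, A = 0: L = 0.0314. Reference rate = (0.5 + 0.0235)/(0.5 + 0.0157) = 1.0152. Observed IRR = 1.5/1.0152 = 1.478. With A = 0.0098 it is 1.472.

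| Share imputed *m* | Exposed time lost | Observed IRR, *r* = 0.115 | Observed IRR, *r* = 0.50 |
|---|---|---|---|
| 5% | 1.6% | 1.496–1.498 | 1.486–1.489 |
| 10% | 3.1% | 1.492–1.497 | 1.472–1.478 |
| 25% | 7.8% | 1.480–1.492 | 1.434–1.447 |
| 50% | 15.7% | 1.458–1.485 | 1.375–1.405 |

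In each cell the lower value assumes that no over-extension is absorbed, and the higher that all of it is.

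**Step 3: does the sample-size statement narrow *r*?** Only indirectly. The protocol says "With an estimated IRR=1.5, n=484 is required with 5% level of significance and 80% power" without an exposed share. The signed-root likelihood-ratio formula is n = (z_a + z_b√B)²/A′. Here d = IRR·r + 1 − r, A′ = 2[(IRR·r/d)·ln IRR − ln d] and B = (ln IRR)²/A′ × IRR·r(1−r)/d². At r = 0.09, d = 1.045, A′ = 0.01673 and B = 1.106, so two-sided n = (1.960 + 0.842×1.051)²/0.01673 ≈ 484. An implied share near 0.09 lies just below the lower end used above, where the bias is smallest. It is a back-calculation, not a stated input.

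**Step 4: with a duration that follows quantity.** In the ideal case where the quantity-based value recovers the true length, L = A = 0 and the IRR stays at 1.50.

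**The case against.** Several stronger readings are tempting, and the protocol does not support them.

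- *Any missing dosage triggers the median.* It does not. A recorded end date or prescribed days comes first. Only prescriptions that lack these and the dosage information are affected, and the protocol does not say how many there are.
- *All supplies receive one pooled value.* The text refers to median values without stating the level. A median within drug, strength and quantity would fit the sentence, and a statistical analysis plan not shown here could set that level. This is why the bias above is conditional. What stands is that the protocol fixes imputation on duration and gives quantity no role in it.
- *No sensitivity analysis bears on this.* Lengthening the treatment periods partly probes truncation. It cannot detect over-extension, which it adds to. It does not separate imputed from recorded durations, and it leaves the primary analysis unchanged.
- *The attenuation is large.* Take people who receive only 56-day supplies, are exposed half the time, and have every prescription imputed at 28 days. The reference rate is then (0.5 + 0.25×2)/(0.5 + 0.25) = 1.333, and a true 2.0 falls to 1.50. That is an extreme subgroup, not a study-level result. With an exposed share of 0.09 and 30% imputed, the lost share is 0.09×0.3×0.5 = 0.0135, the reference rate is (0.91 + 0.027)/(0.91 + 0.0135) = 1.015, and 2.0 becomes 1.97.

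Two further limits also stand. If the 90-day window is applied before each treatment episode, some days lost by truncation become pre-exposure rather than reference time. That spares the reference rate but contaminates the window meant to diagnose confounding by indication. And quantity without dosage does not reveal days supplied exactly, because daily doses vary.

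**Conclusion.** The point holds in a limited form. For prescriptions without a recorded length and without a dosage, the protocol imputes duration and does not say that a recorded quantity is used. If the median is not conditional on quantity, the error depends on supply length and pulls the IRR toward 1. On the assumed mix, a true 1.5 becomes about 1.47 to 1.50 with 10% of prescriptions affected and 1.43 to 1.49 with 25%.

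These figures rest on an assumed median, supply mix and exposed share, on constant rates, and on lost days going to the reference period. The true size cannot be judged from the protocol and is probably small if few prescriptions are affected. The case for the change is that a better rule uses data already held, not that a large bias has been shown.

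**What to change.** In Missing data, write the rule as an ordered list:

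1. Use the recorded end date or prescribed days.
2. Otherwise, use quantity with daily dosage.
3. If quantity is recorded but dosage is not, use the median duration among prescriptions of the same drug, strength and quantity. Optionally, first divide the quantity by the same person's most recent earlier daily units, accepting some error after dose changes. This option cannot help first prescriptions, and it should not draw on later ones, which may depend on the event.
4. Use the drug-specific median only when quantity is also missing.

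Report the share of prescriptions settled at each step, so that readers can judge the size of the issue.

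Add one sensitivity analysis that does not depend on where the event fell. Either leave out everyone with any imputed gabapentinoid duration, or model time from imputed durations as a separate exposure category. Do not leave people out because their event date lies in an imputed window. That removes exposed events while other people's imputed windows remain as event-free exposed time. If everyone has share *m* of exposed time imputed, the IRR is multiplied by about (1 − m): a true 1.5 becomes 1.5×0.90 = 1.35 at 10%, a larger error than the one under test.

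The cost is slightly more complex exposure code, one extra run and some loss of precision in that run. No new data are needed.
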